### Economic evaluation

Client Service Receipt Inventory (CSRI) [40] is a questionnaire for collecting information about use of healthcare and social care services as well as other economic impacts. In our study, we adapted it to take into account the costs due to lost production as well as the cost of medicines, the costs of healthcare use and social care services, and the costs for patient in terms of travelling expenses and time lost. Patients are asked to give details of services and medicines that they have used during the previous 3 months due to depression or for other reasons. Services included hospital care, primary healthcare and social care, as well as the provision of aids, tests and medication. The length of stay is recorded for inpatient episodes, whilst the number of contacts with other services is recorded.

### Sample size

To calculate the sample size it was taken into account that we needed to obtain a difference of at least 17 points in the percentage of medication intake [16]. A total of 194 patients are needed to conduct the study, assuming an alpha risk of 0.05 and a beta risk of < 0.20 and a 20% dropout rate.

### Statistic analysis

Data collected will be analyzed using SPSS-WIN 17.0 and SAS 8.0 statistical analysis software and employs both quantitative and qualitative techniques. Firstly, comparability between the intervention and usual-care groups will be assessed at baseline to check differences.

### Effect evaluation

Data will be primarily analyzed according to the intention to treat principle (ITT), including all participants with valid data regardless of whether they did or did not receive the intervention. In addition, results will be analyzed according to the on-treatment principle. Participants with documented deviations from the protocol (i.e. false inclusions, participants who did not receive the entire intervention or participants in either the intervention or the control group with incomplete follow-up data) will be excluded from the on-treatment analysis. The results of the ITT analysis will be compared with the results of the on-treatment analysis to assess whether protocol violations have caused bias.

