**Economic evaluation**				

Direct and indirect costs	CSRI – adapted	X	X	X

T0 = Baseline, T1 = 3 months after baseline, T2 = 6 months after baseline.

SCID-I: Structured Clinical Interview Axis I DSM-IV; MAQ: Medication Adherence questionnaire; PHQ-9: Patient Health Questionnaire 9-item depression module; EuroQOL-5D: European Quality of Life Scale – 5 domains; STAI-S: State-Trait Anxiety Inventory (State subscale); CSRI: Client Service Receipt Inventory.

Clinical diagnosis is made using the research version of the Structured Clinical Interview for DSM-IV Axis I Disorders (SCID-I) [24,25]. Patients are interviewed in the modules of major depression (present and past), dysthymic disorder, anxiety disorder and adjustment disorder as defined according to DSM-IV criteria. Due to the pragmatic character of the study, GPs are blind to the DSM-IV diagnosis and patient inclusion and follow-up is performed according to their usual practice.

The primary outcome measure of our study is adherence to prescribed antidepressant medications, which is assessed through two methods:

1) pharmacy records: every time a patient buys their medication, the pharmacist registers the date of prescription, the date of dispensation and the number of pills dispensed. At 3 and 6 months from baseline, the patient is asked to present the stock of antidepressant medication and any surplus antidepressants following a GP recommended change in medication. To minimize bias, the patient is not told that the aim is to assess compliance. The pharmacist registers the stock of every medication and the percentage of medication intake is calculated by formula: (Number of doses removed/Number of doses prescribed)*100. Poor adherence is defined as taking less than 80% of the prescribed doses. There are two disadvantages of measuring adherence this way: the patient can remove pills but not take them, and this formula does provide information about the timing of the dose removal.

2) self-reported: adherence to prescribed antidepressant medications is assessed with the 4-item scale developed by Morisky et al [26]. The scale asks patients to respond "yes" or "no" to a set of 4 questions. A positive response to any question indicates a problem with adherence. Patients who respond "yes" to any of the items are categorized as non-adherent.

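### The primary analysis called intention-to-treat is an available-case analysis, and the bias from missing outcomes could be a material share of the 17-point target

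*Protocol article*

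**What the plan says.** Under Statistic analysis, the Effect evaluation section makes an intention-to-treat analysis primary and defines it as "including all participants with valid data regardless of whether they did or did not receive the intervention". It does not say what counts as valid data. A secondary on-treatment analysis drops, among others, "participants in either the intervention or the control group with incomplete follow-up data". The only stated check for bias is this: "The results of the ITT analysis will be compared with the results of the on-treatment analysis to assess whether protocol violations have caused bias".

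Three other sections bear on the point.

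- Sample size aims at "a difference of at least 17 points in the percentage of medication intake" with 194 patients, "assuming an alpha risk of 0.05 and a beta risk of < 0.20 and a 20% dropout rate".
- Measurements builds the intake percentage from two sources. The pharmacist logs each purchase, and at 3 and 6 months "the patient is asked to present the stock of antidepressant medication". Table 2 lists the intake percentage as continuously registered. The second adherence measure, the 4-item self-report scale, has to be answered by the patient at the follow-up visits.
- Enrolment, randomization and allocation has the envelope opened, and the study chart created, only when the patient hands in the prescription at the pharmacy. Patients and pharmacists are not blinded.

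**The concern.** Intention-to-treat has two parts: patients are analysed in the arm to which they were allocated, and all randomised patients are kept. The definition secures the first and gives up the second. The article itself fixes this rule for the primary analysis, so it is not a detail left to an analysis plan.

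The outcome is adherence. A patient who abandons the medication has little reason to return to the pharmacy with leftover stock or to attend the interview, so patients without valid data may well be poorer adherers. The programme adds unblinded pharmacist contacts at pharmacy visits, which could change who returns and make the loss differ between arms. Nothing in the stated rule protects the comparison against that.

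The stated check would not show it. A patient with no outcome data is absent from both the primary and the on-treatment sets, so close agreement between the two would reassure wrongly. The consequence extends beyond the primary result: adherence is also the effect measure in the incremental cost-effectiveness ratio, and the Discussion ties a recommendation to implement the programme to these findings.

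**Working it through.** **Inputs from the protocol article.** Total 194, ratio 1:1, dropout 20%, target 17 points of intake, alpha 0.05, power at least 80%. Not given: dropout by arm, adherence of dropouts, the standard deviation, and the meaning of valid data. Intake is taken to run from 0 to 100.

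**The plan's own figure.** The expected loss is 0.20 × 194 = 38.8, about 39 patients, leaving 0.80 × 194 = 155.2, or about 77.6 per arm. Without a standard deviation, 194 cannot be reproduced from the article alone. It is compatible with a two-sided comparison of means and a standard deviation near 37.5 to 38, which gives 193 to 198 after dividing by 0.8. No error in the sample size is shown, and the point does not depend on it.

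**Formula.** In each arm, let m be the proportion missing and g the mean intake of observed patients minus that of missing patients. The all-randomised mean is the observed mean minus m × g. Hence:

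bias = available-case difference − all-randomised difference = m(I) × g(I) − m(C) × g(C), with I for intervention and C for control.

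**Assumed scenarios around an observed difference of 17.** Loss averages 20% in all of them.

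| Missing I / C | Assumption on missing patients | Bias | All-randomised difference |
|---|---|---|---|
| 20% / 20% | same gap in both arms | 0 | 17 |
| 20% / 20% | all at 0, so each gap equals the arm's observed mean | 0.2 × 17 = +3.4 | 0.8 × 17 = 13.6 |
| 15% / 25% | gap 50 | 7.5 − 12.5 = −5 | 22 |
| 10% / 30% | gap 40 | 4 − 12 = −8 | 25 |
| 10% / 30% | gap 60 | 6 − 18 = −12 | 29 |
| 30% / 10% | gap 40 | 12 − 4 = +8 | 9 |
| 30% / 10% | gap 60 | 18 − 6 = +12 | 5 |

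The sign follows the arm that loses more patients. Greater loss in control understates the programme's effect; greater loss in intervention overstates it.

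**Direct check of the third row's bias.** Let observed patients average 80 and missing patients 30 in both arms. The all-randomised means are 0.85 × 80 + 0.15 × 30 = 72.5 for intervention and 0.75 × 80 + 0.25 × 30 = 67.5 for control. The true difference is 5, while the available-case analysis reports 80 − 80 = 0.

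**As a share of the target.** 3.4/17 = 20%, 5/17 = 29%, 8/17 = 47%, 12/17 = 71%.

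**What a 17-point bias would take.** With 20% missing in each arm, the gaps would have to differ between arms by 17/0.2 = 85 points. With a common gap of 60, dropout would have to differ by 17/60 = 28 percentage points; with a gap of 80, by 17/80 = 21.

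**The case against.** The strongest reply is that purchases are registered continuously. A patient who stops buying still leaves a record of low dispensing and may count as having valid data. If so, many who discontinue stay in the analysis. This stands in part. Because valid data is not defined, a reader cannot tell whether a patient with a dispensing record but no stock count is kept. The article nowhere says that missingness depends on adherence; that is an inference from how the outcome is collected. For the same reason, it is not shown that the analysis merely compares persisters with persisters.

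Loss before the envelope is opened, from prescriptions never filled, should also balance between arms on average. That is right, but it does not cover later loss.

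A reader might infer that this is a complete-case analysis. The text does not support that. Incomplete follow-up is a separate ground for exclusion from the on-treatment set, which would be pointless if the primary set had already removed such patients. The primary set appears to keep partial data.

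A reader might also infer that the bias can exceed the 17-point target. With 20% missing per arm, worst-case bounds put the all-randomised difference at 0.8 × 17 ± 20, that is −6.4 to 33.6. The lower bound needs every missing intervention patient at 0 and every missing control patient at 100, which contradicts the idea that missing patients are poor adherers in both arms. Another route is 30% intervention and 10% control loss, all missing at 0, with observed means of 77 and 60: 0.7 × 77 − 0.9 × 60 = −0.1, a bias of 17.1. These cases are arithmetically possible but extreme, and nothing in the article points to them.

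Finally, the choice of imputation model and sensitivity analyses is commonly left to an analysis plan, and their absence from an article is no fault. The criticism is confined to the rule that the article does state, its label, and a check that cannot do what is needed.

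**Conclusion.** The point holds in this form: the primary analysis carries an intention-to-treat label but, by the article's own definition, is an available-case analysis. The comparison with the on-treatment analysis cannot detect bias from patients with no outcome, because neither set contains them.

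The size is conditional. If loss is 20% in both arms and missing patients are poor adherers in both, the bias is small, 0 to 3.4 points in the cases worked. If loss differs by arm, it is 5 points for a 25% versus 15% split with a 50-point gap, and 8 to 12 points for a 30% versus 10% split with a 40 to 60 point gap. That is roughly 30% to 70% of the target effect, in either direction. These results rest on assumed dropout by arm and assumed adherence of dropouts. They show that the bias can be material, not that it will be.

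**What to change.** - Define the primary set as all randomised patients analysed as allocated, and say whether a patient whose envelope was never opened counts as randomised.
- Define valid data. Where stock is not presented, use the continuous dispensing record, so that documented non-collection counts as low intake.
- Handle what is still missing by multiple imputation or a likelihood-based model that uses baseline and 3-month data.
- Relabel the current rule available-case and keep it as a sensitivity analysis.
- Add a sensitivity analysis that counts patients with no valid data as non-adherent on the 80% cut-off. It may misclassify adherent patients who merely missed a visit, and it is binary whereas the sample size rests on percentage intake, so it should support the primary result and not replace it.

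The cost is a change of wording and modest extra analysis work, with possibly a slightly wider confidence interval. No new data collection is needed, since the dispensing record is already kept.

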### Intervention and usual care

Patients in the intervention group will receive the support programme in community pharmacy (PRODEFAR) every time they go to the pharmacy to pick up the medication or to ask for counselling in the course of the 6 months of the study. Pharmacists participating in the study received 8 hours of training about PRODEFAR prior to the study. The training followed a manual created for the study and is accredited by the Catalonian council of continuous pharmaceutical training (*Consell Català de la formació farmacèutica contínua*) (Reference Number: 09F00676).

PRODEFAR consists of a series of educational interventions focused on improving patients' knowledge of antidepressant medication, as well as making patients aware of the importance of compliance to the medication. Moreover, in patients with a sceptical attitude towards the medication, the intervention will aim to reduce stigma, reassure the patient about possible side-effects, and stress the importance of carrying out GPs' advice. First contact in the PRODEFAR is expected to take between 20 and 30 minutes, subsequent interventions are expected to take between 10 and 15 minutes.

Regardless of whether participants belong to the intervention group or not, they receive the usual pharmaceutical care as well as the treatment considered most appropriate by their physician. Patients receiving usual care get ordinary advice about medication when collecting it. Any concerns and questions addressed to the pharmacist are also answered.

Patients in the intervention group are asked to avoid conversations concerning the PRODEFAR with patients from the control group. The importance of this requirement is emphasised to patients from both groups at baseline assessment.

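### The on-treatment exclusion for an incomplete programme applies to one arm and tracks adherence, so its gap from ITT cannot show whether protocol violations caused bias

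*Protocol article*

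**What the plan says.** The Effect evaluation section makes ITT primary: "Data will be primarily analyzed according to the intention to treat principle (ITT), including all participants with valid data". It adds an on-treatment analysis that leaves out false inclusions as well as "participants who did not receive the entire intervention or participants in either the intervention or the control group with incomplete follow-up data". The two sets of results are then to be compared "to assess whether protocol violations have caused bias".

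The Intervention and usual care section says that intervention patients receive the programme "every time they go to the pharmacy to pick up the medication or to ask for counselling" during the six months. It sets no number of sessions. Control patients get ordinary advice at collection and have no programme to complete.

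The Measurements section states: "The primary outcome measure of our study is adherence to prescribed antidepressant medications". There are two measures. The first relies on dispensing data: "every time a patient buys their medication, the pharmacist registers the date of prescription, the date of dispensation and the number of pills dispensed". Stock is also counted at 3 and 6 months, and intake is calculated as "(Number of doses removed/Number of doses prescribed)*100". The second is a four-item self-report scale.

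**The concern.** The visit at which a session is delivered is usually also the visit at which dispensing is recorded. An intervention patient who stops collecting medication misses sessions and will tend to score low on adherence. Excluding that patient for an incomplete programme is selection after randomisation on something close to the outcome. No control can be excluded on the same ground. The follow-up criterion is worded for both arms, but the programme criterion can operate in only one.

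The on-treatment difference is therefore expected to lean towards the programme even if the programme does nothing. The plan nevertheless treats the distance between the two analyses as informative about bias from protocol violations. That distance mixes any real consequence of violations with the selection that the exclusion itself creates, and it cannot separate them. At stake is how a trial with a null or modest ITT result would be read beside a larger on-treatment figure.

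**Working it through.** **Plan's own figure.** The sample size of 194 cannot be reproduced, because the article gives neither an SD nor a base rate. This point does not depend on it. Only the number per arm is used: 194 × 0.8 / 2 = 77.6, taken as 78.

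**From the article:** planned difference 17 points, 20% dropout, 1:1 allocation, programme at pharmacy visits, six-month course.

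**Assumed (not in the article):** true effect zero; intake Beta-distributed with mean *m* of 70 or 80% and SD *s* of 25 or 30 points; six monthly pick-ups; number attended *K* ~ Binomial(6, intake); an intervention patient is kept only if *K* ≥ *t*.

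**Formulas.** With *m* and *s* as fractions, α + β = m(1 − m)/s² − 1 and α = m(α + β). Mean intake given *K* = *k* is (α + k)/(α + β + 6). The false difference is the mean intake among those with *K* ≥ *t*, minus *m*.

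**Worked case (m = 0.70, s = 0.30, t = 4).** α + β = 0.21/0.09 − 1 = 1.333, so α = 0.933 and β = 0.400. The proportion kept is 0.679 and their mean intake is 86.7%. The false difference is 86.7 − 70.0 = 16.7 points.

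**False difference in points, no controls excluded:**

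| Pick-ups required | 70%, SD 30 | 70%, SD 25 | 80%, SD 30 | 80%, SD 25 |
|---|---|---|---|---|
| ≥1 | 4.4 | 2.0 | 5.0 | 2.0 |
| ≥2 | 8.6 | 4.9 | 8.2 | 4.4 |
| ≥3 | 12.7 | 8.5 | 10.9 | 7.1 |
| ≥4 | 16.7 | 12.5 | 13.4 | 9.9 |
| ≥5 | 20.6 | 16.9 | 15.6 | 12.8 |
| all 6 | 24.5 | 21.5 | 17.7 | 15.9 |

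The range is 2.0 to 24.5 points. In simulated t-tests at mean 70%, SD 30 and 78 per arm before exclusion, the true null is rejected in about 16% of trials with ≥1, 48% with ≥2 and 98% with ≥4.

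**Offset from the two-arm follow-up exclusion.** Suppose that half of the controls with fewer than 4 pick-ups are also dropped (assumed). In the worked case:
- Share with fewer than 4: 1 − 0.679 = 0.321. Their mean intake: (70 − 0.679 × 86.7)/0.321 ≈ 34.7%.
- Control mean after dropping half of them: (0.679 × 86.7 + 0.1605 × 34.7)/(0.679 + 0.1605) ≈ 76.8%.
- False difference: 86.7 − 76.8 = 9.9 points, with rejection in about 69% of trials.

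The selection shrinks but does not vanish.

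**Looser link between sessions and intake.** Let ρ be the correlation between sessions and intake, and drop the lowest fraction *f* on sessions. The shift is ρ × SD × φ(c)/(1 − f), with c the *f*-quantile of the standard normal. For ρ = 0.5, SD 25 and f = 0.2 this is 0.5 × 25 × 0.280/0.8 = 4.4 points. Over ρ = 0.3 to 0.7, f = 0.1 to 0.4 and SD 25 to 38, it runs from 1.5 to 17.1 points. The SD of 38 is about the value at which 78 per arm gives 80% power for 17 points, two-sided: 17/(2.80 × √(2/78)) ≈ 37.9.

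In every scenario the sign favours the programme, and the corresponding ITT difference has expectation zero.

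**The case against.** Several points on the other side are fair.

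- **ITT is primary.** A reader might infer that the trial's main result is biased. It is not: the exclusion touches only the additional analysis. This limits the severity.
- **A complete programme is not defined.** Because the programme is given at each visit made, a patient who comes twice and receives it twice could count as complete. On that reading the selection would be much weaker, and the table would not apply. The definition may stand in a fuller document. The size therefore has to be given as a range, and no single scenario, such as 4 of 6 pick-ups, can be the headline.
- **Controls can be excluded too.** It is tempting to say that equally non-adherent controls all stay in. The follow-up criterion covers both arms, and a control who stops visiting may lack a stock count. The offset is real but complete only if all such controls are lost.
- **Collection is not the outcome itself.** Intake is doses removed over doses prescribed, with stock counts and a self-report scale alongside. Counselling visits also deliver the programme. The link is looser than the binomial model makes it; the correlation-based range allows for this.
- **The text states no directional conclusion.** A reader might infer that the plan commits its authors to reading a larger on-treatment effect as a real effect masked by non-compliance. It says only that the results will be compared to assess bias. That misreading is possible but not prescribed.

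What survives is that a gap is expected without any bias in ITT, so the comparison cannot do what the plan asks of it.

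**Conclusion.** The concern holds for the secondary analysis and for the inference attached to it. One exclusion criterion can apply only to the intervention arm and is tied to the visits that feed the adherence measure. With no true effect, the on-treatment analysis can favour the programme by about 2 to 25 points before any offset, against a planned effect of 17. These figures are illustrative: they assume mean intake of 70–80%, SD 25–30, six pick-ups, and a complete programme defined by a minimum number attended. Loss of comparable controls, a looser link or a lenient definition would reduce them. The direction is firm wherever missed sessions go with low adherence; the size is not. Severity is moderate.

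**What to change.** 1. Delete the sentence that uses the comparison of the two analyses to judge bias, or state that a difference between them is not evidence of bias in ITT.
2. Replace the one-arm exclusion with a complier-average (instrumental-variable) estimate, using randomised allocation as the instrument: the ITT difference divided by the difference between arms in the proportion receiving the programme. Define receipt in advance, for example as at least one session. Count any programme delivery to controls as receipt, since the Discussion section itself names that contamination as a risk.

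The cost is a wording change and one standard analysis. It needs a record of who received the programme, which the on-treatment analysis already requires for the intervention arm; delivery to controls would have to be noted as well. The interval will be wider than for ITT. If nearly every intervention patient has a first contact and few controls receive the programme, the estimate will lie close to ITT and add little.
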